#### Hypnotherapy through self-exercises on CD

Children assigned to the CD-group are visited at home by a specially trained research nurse. During this visit the research nurse explains the nature of HT and the exercises to the child and parent(s) and children receive the CD together with an instruction leaflet. In addition, children and parent(s) are instructed not to talk about the abdominal pain anymore. Children are asked to do the first exercise of the CD during this visit, to check whether the child understands the given instructions. The previous trial on home-based treatment has demonstrated that this method is very easy to understand and use [28]. The CD contains five standard scripts of the hypnosis exercises, which are identical to the exercises used by the hypnotherapists. These exercises consist of one exercise on breathing and progressive relaxation and four visualization exercises: ‘the favorite place exercise’, ‘the rainbow planet/air balloon exercise’ (depending on developmental age), ‘the beach without worries exercise’ and ‘the slide exercise’). Two separate CDs are used to make sure that the language used is adapted to the child’s developmental age: one CD for children visiting primary school and one CD for children visiting secondary school. Prior to this RCT, the CD has been tested by three children with chronic abdominal pain and no changes were required. Children are instructed to listen to the hypnosis exercises at least five times a week over a period of three months. Furthermore, they are encouraged to practice the breathing exercise a few times a day. The frequency of listening to the CD will be recorded by the participants in their instruction leaflet. The research nurse will make phone calls to the children after 4 and 8 weeks of treatment to stimulate treatment compliance.

#### Co-interventions

All children participating in this RCT are seen by their pediatrician or pediatric gastroenterologist after three months of HT to evaluate the effects of HT and to provide standard medical care if considered necessary. In addition, children will also visit their physician after 6 months of follow up if necessary.

### Outcomes

Outcomes are measured at baseline (T0), after 3 months of therapy (T1) and at 6 and 12 months follow-up after the end of therapy (T2, T3).

Outcomes are recorded by patients and/or parents at home. At inclusion, a questionnaire on demographics and clinical features is filled out by the treating physician. An overview of the assessments made in this RCT is shown in Table 1.

**Table 1 T1:** Overview of outcomes

**Outcome**	**Instrument**	**T0**	**4 wks**	**8 wks**	**T1**	**T2**	**T3**
Abdominal pain	Abdominal pain dairies	X	X	X	X	X	X
Hypnotic susceptibility	Stanford hypnotic clinical scale for children	X					
Treatment expectations	Self-designed questionnaire for child and parents	X					
Depression and anxiety	Revised Anxiety and Depression Scale-short version (RCADS-25)	X			X	X	X
Somatization	Children’s Somatization Inventory (CSI)	X			X	X	X
Health related quality of life	KIDSCREEN-52	X			X	X	X
Pain beliefs	Pain Beliefs Questionnaire (PBQ)	X			X	X	X
Coping strategies	Children’s Coping Strategies Checklist-revision 1 (CCSC-R1)	X			X	X	X
Cost-effectiveness/cost-utility	Health Utility Index Mark 3 (HUI-3) & costs-questionnaire	X			X	X	X
Adequate relief	Binary question on adequate relief				X	X	X

1. Abdominal pain

The main goal of treatment in IBS/FAP(S) patients is a reduction in levels of abdominal pain.

Abdominal pain is assessed with a diary, in which children record the frequency and intensity of abdominal pain episodes on seven consecutive days [14,24,27,31]. *Pain frequency* is recorded in minutes of abdominal pain per day and is scored as 0 when there was no pain, 1 if children experience 1-30 minutes of pain, 2 for 31-120 minutes of pain and 3 if abdominal pain lasts more than 120 minutes. A pain frequency score (PFS) is subsequently calculated by summing the scores of the seven days, giving a maximum PFS of 21 [24,27,31]. *Pain intensity* is scored using an affective facial scale with faces ranging from showing no pain at all (face A) to the most severe pain (face I). Scores on the facial scale are transported to a daily 0-3 score. No abdominal pain is scored as 0, faces A-C are scored as 1, faces D-F score 2 and faces G-I score as 3. Again, scores of seven days are totaled giving a pain intensity score (PIS), with a maximum of 21 [24,27,31].

The primary outcomes in this RCT are the proportion of patients in which treatment is successful at the end of treatment and the proportion of successfully treated patients after 1 year follow-up. Treatment success is defined as at least 50% reduction in both abdominal pain frequency and intensity scores.

2. Hypnotic susceptibility

Hypnotic susceptibility is defined as a generalized tendency to respond to hypnosis and hypnotic suggestions [32] and is assessed using a Dutch translation of the Stanford hypnotic clinical scale for children [33]. It is administered by the treating hypnotherapist in children assigned to the HT-group and by the research nurse in children assessed to the CD-group. The Stanford hypnotic clinical scale for children consists of seven items. Scores are based on assessment of the child’s behavior and experiences which are verbally reported to the therapist/research nurse. Scores on this scale range from 0 to 7 and higher scores represent higher hypnotic susceptibility.

3. Treatment expectations

Expectations about the response to treatment are assessed for the child, mother and father separately. Child and parents are asked whether they expect the child to improve with treatment and this question is scored on a 11-point scale (0 = not at all; 10 = complete recovery). It is also assessed whether they have a (strong) preference for HT with a therapist or home-based with CD.

4. Depression and anxiety

The short version of the Revised Anxiety and Depression Scale (RCADS-25) is a valid and reliable instrument for the Dutch population to assess symptoms of depression and anxiety [34]. It contains five subscales measuring symptoms of generalized anxiety disorders, separation anxiety disorder, social phobia, panic disorder and major depressive disorder. Each subscale consists of five items, which are scored on a 0 to 3 scale (0 = never; 3 = always). A total score on anxiety is calculated by summing scores on the four individual anxiety scales.

5. Somatization

Child somatization scores are assessed using the Dutch version of the Children’s Somatization Inventory (CSI), which has been shown to be a reliable and valid self-report instrument in children and adolescents [35]. It contains 35 items on the extent to which children experienced somatic symptoms in the previous two weeks. Items are scored on a 5-point scale, ranging from 0 (=not at all) to 4 (=a whole lot). A total score is calculated by summing all 35 individual items and higher scores reflect a higher intensity of somatic complaints experienced by the child. A separate CSI-score for non-gastrointestinal (GI) symptoms can be calculated by leaving out 7 items on GI-complaints: nausea, constipation, diarrhea, epigastric and abdominal pain, vomiting and bloating. To assess GI-complaints other than abdominal pain, items on all GI-symptoms but abdominal pain are summed.

6. Health related quality of life

The KIDSCREEN-52 questionnaire is a frequently used and reliable instrument to measure health related Qol in children and adolescents and has been validated in Dutch pediatric patient groups [36,37]. It contains items on ten dimensions of health related QoL: physical well-being, psychological well-being, moods and emotions, self-perception, autonomy, relations with parents and home life, social support and peers, school environment, social acceptance (bullying) and financial resources. A 5-point Likert scale is used to score each item. Rasch scores for each individual dimension are computed from the individual items and these are transformed into T-values. Higher T-values indicate a better health related QoL and well-being.

7. Pain beliefs

Negative and positive beliefs that children have about their abdominal pain are assessed using the Pain Beliefs Questionnaire (PBQ). A Dutch translation of the PBQ, which is reliable and validated in children and adolescents is used [38,39]. The PBQ consists of 32 items scored on a 5-point Likert scale. Negative beliefs can be divided into five subscales, namely condition frequency, condition duration, condition seriousness, episode specific intensity and episode specific duration. The negative beliefs scale is calculated by summing all 20 items on negative beliefs. The other 12 items assess problem focused coping potential (PFCP) and emotion focused coping potential (EFCP). The PFCP and EFCP scales are computed by averaging the 6 items belonging to both scales. Higher scores on a scale indicate that a child has such thoughts more frequently.

8. Coping strategies

The Dutch version of the Children’s Coping Strategies Checklist-revision 1 (CCSC-R1) is used to measure strategies for coping with everyday problems [40,41]. The CCSC-R1 includes 54 items, all starting with the same phrase ‘if I have a problem…’ and all items are scored on a 4-point Likert-scale (1 = never; 4 = always). This questionnaire has sound psychometric properties and comprises five dimensions: problem focused coping, positive cognitive reframing, distraction strategies, avoidance strategies and support seeking strategies. Scale scores on all five dimensions are calculated by averaging the individual items belonging to the five scales.

9. Cost-effectiveness/cost-utility

The Health Utility Index Mark 3 (HUI-3) is applied as a multi-attribute utility measure of health status and will be used in the cost-effectiveness and cost-utility analysis. It is suitable for assessing children, but because children may be too young to provide reliable and valid information about their own health status, proxy measurements are taken from parents [42-45]. The health utilities derived from the HUI-3 have been anchored with 1 indicating perfect health and 0 indicating death. Quality adjusted life years (QALY) will be calculated by taking the sum of the utility of health states over time by the time in between successive measurements.

In addition to the HUI-3, the Dutch Health and Labor Questionnaire (HLQ) has been adapted to the study setting to measure the direct and indirect costs of health care utilization, work absenteeism by parents, and school absenteeism by children.

10. Adequate relief

Adequate relief has been shown to be a well validated outcome measurement in trials on treatment for IBS [46]. Parents are asked whether their child has adequate relief of IBS-related abdominal pain or discomfort, using a dichotomous scale (yes/no).

### Statistical analysis

Two hundred and sixty children diagnosed with IBS or FAP(S) will be included. The data will be analyzed following the intention to treat principle. The primary analyses will focus on the proportion of patients in both treatment arms in which treatment was successful (>50% reduction abdominal pain frequency and intensity) at T1 and the proportion of patients in which treatment was successful at T3. In addition, abdominal pain levels will be compared in its continuous form using all five moments of measurement during follow-up (after 4 and 8 weeks of treatment, at T1, T2 and T3). These data will be analyzed using linear mixed models to account for correlations of measurements within the same individual. Similar longitudinal, repeated measurement analyses will be performed for the secondary outcomes including depression and anxiety, somatization, health related Qol, pain beliefs, coping strategies and adequate relief. Baseline values will be incorporated in these analyses to adjust for any imbalance at baseline despite randomization and to increase precision by removing between-person variability.

Two explanatory subgroup analyses are planned to evaluate whether there are indications that treatment effects differ between clinical subgroups. Children diagnosed with IBS will be compared to children with FAP(S). Additionally, children in pre-puberty age (13 years or younger) will be compared to older children, since our previous RCT showed that younger children showed a better treatment response up till 6 months after treatment [24].

Economic evaluation will be performed from a societal perspective. Cost-effectiveness and cost-utility ratios will be calculated for the additional costs per extra patient with at least 50% reduction of abdominal pain scores and the additional costs per extra QALY.

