#### Individual hypnotherapy by a therapist

Individual HT consists of six sessions of 50-60 minutes over a period of three months and is carried out by 11 hypnotherapists affiliated to the recruiting hospitals. All participating hypnotherapists are qualified and have many years of experience in performing HT in children. They have been trained in working with the treatment protocol and instructed to use the same scripts that are used in the CD group, but are allowed to adapt contents and order of these scripts to the child’s interests and specific issues that may come up during therapy. The same protocol is used for children of all ages, but the language used is adapted to the child’s developmental age.

In the first HT session, therapists take a full history. Furthermore, it is explained to both child and parent(s) what hypnotherapy is and how it can help in reducing chronic abdominal pain.

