#### Power

The primary analysis focuses on the proportion of patients with at least 50% reduction in abdominal pain levels compared to baseline at the end of therapy and after one year of follow up. Based on previous trials, we made a conservative estimate of this percentage being around 75% in the group receiving HT performed by a therapist. In the group assigned to self-hypnosis with CD, we anticipated this percentage to be marginally lower at 65%. In order to be a reasonable alternative treatment, this percentage should not become lower than 50% in the CD group. This non-inferiority margin should be viewed in relation to success rated with standard medical care of around 30-40% in previous trails [23,24,28]. Based on these expected proportions and a non-inferiority margin at 50%, a total of 115 patients per group are needed to achieve a power of 80% with a one-sided significance level of 5%. Since we expect less than 10% drop-out, our aim is to include 130 patients per group.

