## Discussion

To our knowledge, this is the first RCT comparing the effectiveness of gut-directed HT performed by a qualified therapist to home-based HT with self exercises in CD in children with IBS or FAP(S). It has been designed according to methodological recommendations on the design of treatment trials for gastrointestinal disorders and has several strengths [29]. A total of 260 children with a Rome III diagnosis of IBS or FAP(S) are included in this RCT, while previous pediatric trials on HT had sample sizes up to 52 patients [23-25,28]. Generalizability of the results of this trial will be increased, because we include both younger children and adolescents, patients from urban and rural areas in the Netherlands and recruit children from both academic centers and teaching hospitals. In addition, children are followed for a period of 1 year after the end of therapy, to evaluate whether initial effects are sustained over time. In contrast with our earlier HT trial, in which all children were treated by the same hypnotherapist [24], in this study eleven different hypnotherapists are involved in the treatment of children with abdominal pain. This will shed light on the influence of the therapist with regards to efficacy. By assessing secondary outcomes, such as depression, anxiety and somatization, it may become possible to predict response to HT, thereby allowing clinicians to select children that are likely to benefit from HT. A possible limitation of this study may be the fact that children and parents are not blinded for the received treatment, which is not possible due to the nature of HT. Recording of outcome measures by children and parents themselves at home, instead of recording of outcomes by a health care professional during a visit to the hospital, however, reduces the risk of detection bias. In addition, the fact that symptoms of abdominal pain are recorded for seven consecutive days has the benefit that it corrects for individual variability of symptoms over time. Response expectancies are known to (partly) mediate effects of psychological treatments, such as HT [47]. We therefore record expectancies about HT from the child and both parents separately to assess the magnitude of expectation bias. Another possible limitation of the design of this RCT may be the fact that we did not include a third treatment arm with children receiving standard medical care. This third treatment group however was waived, since reviewers considered it being not ethical to abstain children from treatment with HT, because previous studies have shown HT to be superior to standard medical care in this group of patients [23,24,28].

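### Eleven therapists deliver one arm only, and neither the sample size nor the described analysis shows any allowance for therapist clustering; if the therapist ICC is 0.02 to 0.10, power at 115 per arm is about 77% to 67%

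*Protocol article*

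**What the plan says.** **Delivery (Protocol article, Individual hypnotherapy by a therapist; Hypnotherapy through self-exercises on CD).** Treatment in the therapist arm "is carried out by 11 hypnotherapists affiliated to the recruiting hospitals". The therapists are trained in the protocol and told to use the CD scripts, but may change what the scripts contain and their sequence to suit the child. The CD arm gets fixed recordings, a home visit by a research nurse and two telephone calls. Therapist clusters therefore exist in one arm only.

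**Sample size (Power).** For the therapist arm, "we made a conservative estimate of this percentage being around 75% in the group receiving HT performed by a therapist". For the CD arm, "we anticipated this percentage to be marginally lower at 65" per cent. The calculation is introduced by "Based on these expected proportions and a non-inferiority margin at 50" per cent, and its result is that "a total of 115 patients per group are needed to achieve a power of 80% with a one-sided significance level of 5" per cent. Then: "Since we expect less than 10% drop-out, our aim is to include 130 patients per group". The section mentions neither an ICC nor a design effect.

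**Analysis (Statistical analysis).** The primary analyses compare success proportions at the end of treatment and at one year, with no test or model named. For the continuous pain scores, "These data will be analyzed using linear mixed models to account for correlations of measurements within the same individual"; similar models are planned for the secondary outcomes. The two planned subgroup analyses concern diagnosis and age.

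**Discussion.** On using eleven therapists where the group's earlier trial used one, the authors write: "This will shed light on the influence of the therapist with regards to efficacy".

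**The concern.** Children treated by the same therapist may have more similar outcomes than children treated by different therapists. If so, the therapist arm holds less information than its head count suggests, while the CD arm is unaffected. The uncertainty of the difference in success proportions then depends partly on how much eleven therapists vary.

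There are two possible consequences, depending on the analysis. If it allows for the clustering, the interval is valid but power is below the figure obtained for independent children. If it ignores the clustering, the interval is too narrow and the chance of wrongly declaring non-inferiority exceeds 5%. The second matters more here, because the Discussion names introduction of the home treatment into clinical care as the next step after a favourable result.

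The article also presents therapist influence as something the trial will inform, while its power figure is the one obtained when that influence is zero.

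**Working it through.** **Inputs.** From Power: success 0.75 (therapist) and 0.65 (CD), lower limit 0.50 for CD, one-sided 5%, power 80%, 115 evaluable and 130 enrolled per group, drop-out below 10%. From the description of the therapist arm: 11 therapists. The limit is read as a margin of 0.75 − 0.50 = 0.25, the reading that reproduces the stated number. The ICC is not in the document; 0.02, 0.05 and 0.10 are assumptions, as are equal caseloads.

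**Step 1: reproduce the plan's figure.** The variances are 0.75 × 0.25 = 0.1875 and 0.65 × 0.35 = 0.2275, summing to 0.415. The distance from the expected difference to the margin is 0.25 − 0.10 = 0.15.

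n = 0.415 × (1.645 + 0.842)² / 0.15² = 114.03, rounded up to 115, as stated. This formula treats all children as independent. Power at 115 is 80.3%.

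**Step 2: add clustering in the therapist arm only.** With n per arm, the mean caseload is m = n/11 and the design effect is DE = 1 + (m − 1) × ICC.

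SE = √[(0.1875 × DE + 0.2275)/n]; power = Φ(0.15/SE − 1.645).

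At n = 115, m = 115/11 = 10.45. For ICC 0.05: DE = 1 + 9.45 × 0.05 = 1.47; SE = √[(0.1875 × 1.473 + 0.2275)/115] = 0.0662; power = Φ(2.267 − 1.645) = 73.3%.

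| ICC (assumed) | DE, n = 115 | SE increase, n = 115 | Power, n = 115 | Power, n = 117 | Power, n = 130 |
|---|---|---|---|---|---|
| 0 | 1.00 | none | 80.3% | 80.9% | 84.4% |
| 0.02 | 1.19 | 4% | 77.4% | 78.0% | 81.3% |
| 0.05 | 1.47 | 10% | 73.3% | 73.8% | 76.9% |
| 0.10 | 1.95 | 20% | 67.2% | 67.6% | 70.2% |

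The 117 column is 130 × 0.90, the plan's own drop-out bound. The 130 column assumes that every enrolled child is evaluable.

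**Step 3: the ICC at which power equals 80%.** The required SE² is (0.15/2.487)² = 0.00364. Solving for the ICC gives about 0.002 at 115 per arm, 0.006 at 117 and 0.029 at 130. For 130: 0.00364 × 130 = 0.473; (0.473 − 0.2275)/0.1875 = 1.31; 0.31/(11.82 − 1) = 0.029.

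**Step 4: error of a test that ignores clustering.** At the non-inferiority boundary (75% v 50%) the CD variance is 0.25. The error is 1 − Φ(1.645 × √[0.4375/(0.1875 × DE + 0.25)]). At 115 per arm this gives 5.7%, 6.7% and 8.3% for ICC 0.02, 0.05 and 0.10.

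**Step 5: sensitivity.** Unequal caseloads make matters worse: with a coefficient of variation of 0.6 in caseload, power at 115 per arm and ICC 0.05 is 70.8%. All figures use normal quantiles; a small-sample correction for 11 therapists would lower power somewhat further.

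**The case against.** A reader might infer that the standard errors *are* too small and that 80% power *is not* delivered. The document does not support that. Both need a therapist ICC above zero, and none is given. At an ICC near zero the plan delivers its power, and at 0.02 the loss is about 3 points. The plan also enrols 130 per group and expects less than 10% drop-out, which leaves some reserve. This objection stands, and the point is conditional for that reason. The reserve does not cover ICCs of 0.05 to 0.10, where power is below 80% even with all 130 evaluable.

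A reader might also infer that the primary analysis is known to treat children as independent. It is not. The sentence about within-child correlation belongs to the continuous outcomes and gives a reason for using mixed models without listing every random effect. No test is named for the primary proportions, and a statistical analysis plan that is not shown could add a therapist term. This also stands. What remains is the sample size, which is complete as published and contains no allowance; a later analysis plan cannot change how that number was obtained.

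Nor does the Discussion show that the authors assume a therapist effect. It poses a question that a null result would also answer.

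Several features may keep the ICC low: training, shared scripts, and a CD of the standard scripts given to every child in the therapist arm. Randomisation is stratified by hospital and the therapists are attached to the hospitals, so adjusting for hospital could absorb part of the variation between therapists. It would not remove the part that acts in the therapist arm alone, and the article names no such adjustment.

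**Conclusion.** The point holds in conditional form. It is certain that therapist clusters exist in one arm only, that 115 per group is the number for independent children, and that the article shows no allowance for therapist clustering. The size of the consequence is not certain, because it depends on an ICC the article does not give.

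For an assumed ICC of 0.02 to 0.10 with eleven equal caseloads, power ranges from about 77% to 67% at 115 evaluable per arm and from about 81% to 70% at 130. The error rates in Step 4 apply only if the primary test ignores therapists. The stated 80% is safe for an ICC up to just under 0.03 with no drop-out, but only up to about 0.006 at the 10% drop-out bound. This is worth correcting because, if clustering is present and ignored, the error favours a non-inferiority claim. It does not show that the trial is underpowered.

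**What to change.** Analyse the primary success proportions and the longitudinal outcomes with a partially nested model: a therapist random effect in the therapist arm only, each CD child as its own cluster, and a small-sample correction for 11 therapists. Report the estimated therapist variance with its uncertainty, which would supply the information the Discussion promises. State an assumed ICC and restate power over 0 to 0.10 at the expected evaluable number.

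**Cost.** No additional children are needed. The treating therapist must be recorded for each child; the article does not say whether this is done. Intervals will be somewhat wider and the power figure less favourable. With 11 clusters of about 10, the therapist variance will be imprecise, particularly for a binary outcome.

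The model protects the validity of the interval; it does not restore lost power. For scale, keeping 80% power with 11 therapists would take 125, 146 or 205 evaluable children per arm at ICC 0.02, 0.05 or 0.10. The restated figure should therefore be presented as a limitation.
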